### Safety

All exercises adopted in this study are very safe and harmless, especially under the guidance of physiotherapists. However, all expected or unexpected adverse events deriving from this study, such as muscle strain or ache, will be recorded and monitored. Moreover, patients subjected to harm from this study will receive free treatment, and any differences in safety between the two groups will be reported by researchers as a part of the results.

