## Methods

### Design

The current study is a single-blind randomized controlled trial, in which patients with KOA will be randomly divided into quadriceps-plus-hip abductor-strengthening group and quadriceps-strengthening group (Fig.1). Importantly, physicians carrying out the assessments will not be informed of the group situation.

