### Outcomes

Participants will be assessed by other physiotherapists blinded to the group allocation at different time points based on different assessments shown in Table 1. Additionally, baseline age, gender, symptoms, disease severity (K-L grade), duration, previous treatment and medication will be recorded using a questionnaire (in week 0). The primary outcome is the overall pain assessed using VAS in the 6th week, while the secondary outcomes include the overall function measured by the Western Ontario and McMaster Universities Osteoarthritis Index (WOMAC), as well as the quality of life assessed by MOS Item Short-form Health Survey (SF-36), and several functional tests.

**Table 1 Tab1:** Schedules for follow-up assessments and date collection

Assessments	Baseline	Active strengthening at home						Follow-up	
	Week 0	1st week	2nd week	3rd week	4th week	5th week	6th week	8th week	12th week
VAS for pain	√	√	√	√	√	√	√	√	√
WOMAC	√						√	√	√
SF-36	√						√	√	√
FTSST	√						√	√	√
Step test	√						√	√	√
Stair ascent/descent task	√						√	√	√
Figure-of-8 Walk Test	√						√	√	√
Adverse effects		√	√	√	√	√	√	√	√

The overall pain intensity in the involved knee within the past 1 week will be self-measured by patients using the VAS, with terminal descriptors ranging from 0 (no pain) to 10 (maximal pain). Meanwhile, the overall function of patients will be assessed adopting WOMAC, a disease-specific scale with high reliability and validity [23]. WOMAC is comprised of 24 items assessing pain (scored 0–20), stiffness (scored 0–8) and physical functions (including personal care, walking, sitting, lifting, sleeping, standing, social life and travelling) (scored 0–68). Every item is rated on a scale of 0–5, with a higher score indicating a worse symptom. Moreover, the quality of life will be measured by SF-36 constituted by eight dimensions, including mobility, pain and discomfort, daily activities, depression and anxiety, and self-care [24].

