Furthermore, the Five Times Sit to Stand Test (FTSST) is used as a simple objective test of lower limb function [25]. To be specific, participants sit on an armless chair with their backs resting against the chair; later, they will be asked to stand up straight and sit down without touching the chair back each time. The test is accomplished upon the fifth time of returning to sitting, and the time spent will be recorded as a result. Besides, the step test is also employed to measure the standing balance [26]. In brief, participants stand barefoot on the diseased leg facing a 15 cm step; subsequently, they step the opposite foot on and off the step as quickly as possible. The frequency completed within 15 s will be recorded as a result, and a higher score indicates a better standing balance function. At the same time, the stair ascent/descent task [27] is also adopted in the current study, in which all participants will be invited to climb up and down a line of stairs, with eight steps one time at their usual speed. The time spent will be recorded as a result, and a longer time suggests a poorer physical function. In the Figure-of-8 Walk Test, the time that participants take to walk a path around 2 cones that is placed 1.5 m apart will be recorded [28]. Patients will be asked to stand in the middle of the 2 cones initially before they walk in a continuous figure-of-8 pattern around the cones. Finally, they will be asked to stop at the location where they begin, and the time spent will be recorded.

Moreover, the adverse effects, medication and other therapies in each participant over the course of trial will be recorded by themselves.

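### The protocol does not agree with itself on which adverse events are recorded or by whom, and its Safety wording asks for a causal judgement before recording

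*Protocol article*

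**What the plan says.** Three places in the protocol article bear on this.

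- **Methods, Safety.** The recording rule is that "all expected or unexpected adverse events deriving from this study, such as muscle strain or ache, will be recorded and monitored". The section also states that "All exercises adopted in this study are very safe and harmless", and it closes with the commitment that "any differences in safety between the two groups will be reported by researchers as a part of the results".
- **Methods, Outcomes, last paragraph.** "the adverse effects, medication and other therapies in each participant over the course of trial will be recorded by themselves". No condition on cause is attached.
- **Methods, Outcomes, Table 1.** A row labelled "Adverse effects" is ticked at weeks 1 to 6, 8 and 12, with no distinction by arm. The sentence introducing the table reads: "Participants will be assessed by other physiotherapists blinded to the group allocation at different time points based on different assessments shown in Table 1".

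On blinding, the Design section says "The current study is a single-blind randomized controlled trial" and that "physicians carrying out the assessments will not be informed of the group situation". The Statistical analysis section adds a blinded statistician. Participants are nowhere listed as blinded, and under Interventions one arm does two exercises and the other does four.

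**The concern.** In a randomised trial the control arm shows the background rate of complaints. Counting every event in both arms and comparing the counts estimates what the added exercises cause, and nobody has to decide the cause of any single event. A rule that admits only events thought to come from the study puts that decision before the comparison. If the person deciding knows the allocation, the decision may be made differently in the two arms.

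Participants may be the ones deciding here, and they know which exercises they do. Someone doing lateral leg raises and pelvic lifts may be readier to link a hip ache to the programme than someone who does neither. Conversely, if participants share the view that the exercises are harmless, they may dismiss a real effect.

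An event that was never written down cannot be recovered at analysis. At stake is the promised safety comparison for exercises that the abstract's Discussion envisages adding to training programmes for knee osteoarthritis if they prove effective.

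**Working it through.** The article states no adverse event figure, so there is nothing to reproduce. The check is a comparison of the text, followed by an illustration on assumed rates.

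**Step 1: the statements side by side**

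| Place | Which events | Who records |
|---|---|---|
| Safety | Those deriving from the study, expected or not | Not stated |
| Outcomes, last paragraph | Adverse effects in each participant; no explicit filter | The participants |
| Outcomes, Table 1 and its introduction | Adverse effects; no explicit filter | Blinded physiotherapists, if the introduction covers every row |

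On which events, Safety carries a causal qualifier and the other two places do not. The words expected and unexpected describe whether an event was foreseen, not whether it is related, so they do not remove the qualifier. On who records, the two parts of Outcomes point to different people. A blinded physiotherapist who only copies the participant's record would inherit whatever the participant had already left out.

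**Step 2: what a filter by cause does**

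Let p be the true event rate, equal in both arms, and let a_E and a_C be the shares of events attributed to the study, and so recorded, in the experiment and control arms.

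- Recorded rates: p × a_E and p × a_C.
- Spurious risk difference: p × (a_E − a_C).

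The arm size is 80 / 2 = 40, from the Sample size section with 1:1 allocation and before dropout. Values of p, a_E and a_C are assumptions; the article gives none. The last column is the exact probability that a two-sided Fisher test at 5% rejects when the true rates are equal.

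| p | a_E | a_C | Recorded E | Recorded C | Difference | Rejects |
|---|---|---|---|---|---|---|
| 20% | 100% | 100% | 20% | 20% | 0 | 2.8% |
| 20% | 50% | 50% | 10% | 10% | 0 | 1.7% |
| 20% | 90% | 60% | 18% | 12% | 6 points | 6.9% |
| 20% | 90% | 30% | 18% | 6% | 12 points | 25.9% |
| 40% | 100% | 100% | 40% | 40% | 0 | 3.0% |
| 40% | 50% | 50% | 20% | 20% | 0 | 2.8% |
| 40% | 90% | 60% | 36% | 24% | 12 points | 15.2% |
| 40% | 90% | 30% | 36% | 12% | 24 points | 64.9% |
| 60% | 100% | 100% | 60% | 60% | 0 | 3.0% |
| 60% | 50% | 50% | 30% | 30% | 0 | 2.8% |
| 60% | 90% | 60% | 54% | 36% | 18 points | 30.2% |
| 60% | 90% | 30% | 54% | 18% | 36 points | 89.8% |

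Swapping a_E and a_C reverses the sign. When a_E equals a_C there is no spurious difference. The distortion therefore needs attribution that differs by arm, which the article neither states nor rules out.

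**The case against.** The best defence is that the article intends broad capture. Outcomes and Table 1 collect adverse effects from every participant on one schedule, no sentence says that unrelated events are discarded, and deriving from the study may loosely mean arising during it. Blinded physiotherapists may be the collectors. Detailed event definitions may sit in the full protocol, which is not shown.

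Much of this stands, and it limits the point. A reader might infer four stronger things that the article does not support:

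- **Events are kept only if attributed to the study.** Safety reads that way taken alone, but Outcomes and Table 1 carry no such filter.
- **Control participants have no exercise to blame for a hip complaint.** Under Interventions both arms do straight leg raises against a resistance band, a movement made at the hip. Attribution may differ by arm, but the contrast is less stark than two exercises against four suggests.
- **Only differences will be shown.** The promise to report any differences does not say that other safety results are withheld.
- **The comparison rests on attribution rather than on randomisation.** That is a possible consequence of one literal reading, not a stated rule.

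The limited precision of 40 per arm is a separate matter: zero events in 40 leaves an exact 95% upper limit of 1 − 0.025^(1/40) = 8.8%, whichever recording rule applies.

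The defence does not remove the disagreement in the text. The one section devoted to safety uses a causal qualifier and soon afterwards speaks of harm from the study. This is something the article states, not a detail it leaves out. If all events were meant, saying so costs nothing.

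**Conclusion.** The point holds as an inconsistency with a possible bias attached. The article does not settle whether all adverse events or only study-caused ones are recorded, or whether participants or blinded physiotherapists record them. On the literal Safety reading, a judgement of cause precedes recording, and participants who know their exercises may make it differently by arm.

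That could bias the between-group safety comparison in either direction. Its size is unknown. Across the assumed rates above, the spurious difference runs from zero with equal attribution to 36 points in the most extreme case, and none of those rates has a source in the article. That participants are unblinded is inferred from the single-blind design and from the visible difference in exercises.

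Priority is lower. Safety is not among the listed primary or secondary outcomes, and the week-6 VAS comparison is unaffected.

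**What to change.** 1. In Safety, replace the restriction to events deriving from the study with a rule such as: *all adverse events occurring after randomisation will be recorded in both arms, whether or not they are thought related to the exercises*. Record relatedness afterwards in a separate field.
2. Reconcile Safety, the last paragraph of Outcomes, and Table 1 with its introduction. State who collects adverse events, and have the same questions asked in both arms at the contacts already scheduled (weeks 1 to 6, 8 and 12). The participant's own record then serves as a supplement. Use one term throughout, either adverse events or adverse effects.
3. Report the number of patients with events by arm, whether or not a difference is seen.

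The cost is a change of wording and a short identical set of questions at existing contacts, with no added visits. The downside is that more minor, unrelated events will be logged.

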## Discussion

A single-blind randomized controlled trial is designed in the current study to examine whether quadriceps combined with hip abductor strengthening is superior to quadriceps strengthening alone in alleviating pain and improving physical function as well as the quality of life of KOA patients.

Researchers and clinicians have attached growing importance to lower limb muscle strengthening, which can be attributed to its effectiveness in reducing knee pain and improving physical function. Moreover, such a phenomenon is also linked to the economical efficiency of lower limb muscle strengthening and the possibility to be widely promoted among patients, especially those in communities. The lower extremities have formed a whole kinematic chain, which makes it impossible for the hip, knee or ankle joints to work completely independent from each other. Instead, they may affect each other.

As is noted in some studies, strength of the hip muscles, especially the hip abductor, may be altered in KOA patients. For instance, a research finds that the isokinetic strength of hip abductor in KOA group is remarkably lower than that in control group [19]. Another study shows that the explosive force and endurance, as well as the isokinetic strength of the hip abductor in KOA group are lower than those in control group [17]. Similarly, it is also found that the hip abductor in KOA patients is reduced by 24% compared with that in normal controls. Meanwhile, the hip abductor muscle strength is negatively correlated with the severity on KOA imaging findings, indicating that the more severe KOA imaging findings are related to the weaker hip abductor strength [16]. Not only the isokinetic strength, but also the isometric strength of hip abductor in KOA patients are smaller than normal, but the difference between two groups is not statistically significant [29]. Typically, the hip abductor plays an important role in stabilizing the trunk and pelvis in gait cycle. Therefore, weakness of hip muscle may lead to changes in the position of body center, resulting in contralateral movement of the pelvis or lateral leaning of the trunk over the standing limb. This would thus increase the magnitude of knee adduction moment, which is an indicator of disease progression. Consequently, it seems that hip abductor appears to have certain impact on knee joint load, which may also play a potential role in the symptoms and progression of disease.

Importantly, limited studies have pointed out that, hip abductor strengthening exercises may be helpful to improve the physical function and alleviate pain in KOA patients.

It was observed that the muscle strength of hip abductor is markedly enhanced, while the WOMAC-pain of knee and FTSST score are distinctly different before and after an 8-week home strengthening program for the hip abductor in 40 KOA patients [19]. Nonetheless, in that study, the patricians in control group are normal persons without KOA. Moreover, a study aiming at KOA patients discovers that, compared with the control group, hip muscle strength, WOMAC- pain, scores of the step test and the stair ascent/descent task are markedly improved in the training group receiving a 12-week hip muscle strength training [20]. It is also found that hip abductor training combined with the quadriceps femoris and hamstring muscle strength training can decrease the WOMAC-pain score in KOA patients by 78% [21] . However, the sample size is as small as 6, and no control group is set up [21]. Moreover, for patients undergoing total knee replacement, the muscle strength of hip abductor is also related to the functional activities (the Figure-of-8 Walk Test, the stair ascent/descent task, and FTSST) in addition to the quadriceps femoris [28]. Those studies have indicated that hip abductor muscle strength training may be beneficial to KOA patients. Therefore, we hypothesize that quadriceps combined with hip abductor strengthening may be superior to quadriceps strengthening alone for KOA patients, and the current study is thereby designed on this account.

Furthermore, the clinical changes in KOA-associated symptoms resulted from hip abductor strengthening intervention will be confirmed using the self-reported pain, as well as subjective measures of function and quality of life. Typically, the common and most widely used tools, including VAS, WOMAC and SF-36, are employed in the current study to measure the changes in symptoms and quality of life in KOA patients.

Besides, four simple tests that can be easily completed in the clinical hospital are selected as the objective measures of function, which have focused on different aspects, including the balance, walking ability, and flexibility. Therefore, the effects of hip abductor strengthening on the improvements of symptoms and quality of life in KOA patients can be evaluated in this study.

## Abbreviations

FTSST: Five times sit-to-stand test
KOA: Knee osteoarthritis
SF-36: MOS item short form health survey
VAS: Visual analogue scale
WOMAC: Western Ontario and McMaster Universities Osteoarthritis Index
